### Statistical Analysis

For the statistical analysis, data normality will be assessed using the Shapiro-Wilk test and Q-Q plots. Descriptive statistics will be performed to characterize the sample. Categorical variables will be presented as absolute and relative frequencies, whereas continuous variables will be expressed as means and SDs or medians and IQRs, in addition to graphical representations. Changes in mean values over time will be represented by delta values (Δ).

The primary analytical model for the 2 primary outcomes (6MWT and TUGT) will be an analysis of covariance, comparing postintervention values between groups while adjusting for the corresponding baseline values. Preintervention and postintervention comparisons will be conducted using the 2-tailed paired Student *t* test for normally distributed variables or the Wilcoxon signed-rank test for nonnormally distributed variables. Between-group differences will be analyzed using the independent Student *t* test for normally distributed variables and the Mann-Whitney *U* test for nonparametric variables.

Effect sizes will be calculated using eta squared (η²) and Cohen *d* and interpreted as small (0.2), medium (0.5), or large (0.8). All losses to follow-up and their respective treatment durations will be recorded for intention-to-treat analysis. All participants will be reassessed after the 12-week intervention period whenever possible. Missing data will initially be explored to determine the pattern and mechanism of missingness. When appropriate, missing outcome data will be handled using multiple imputation methods based on chained equations. Sensitivity analyses will be conducted to compare the results obtained from complete-case analyses and imputed datasets in order to evaluate the robustness and consistency of the findings. In addition, per-protocol analyses will be performed as secondary sensitivity analyses to assess the influence of adherence to the intervention on study outcomes. A significance level of *P*<.05 will be adopted for all statistical tests. Statistical analyses will be performed using the SPSS, version 25.0 (IBM Corp) [51], and graphs will be generated using R software (R Foundation for Statistical Computing) [52].

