### Randomization

After the completion of eligibility screening and baseline assessments, participants will be randomly allocated in a 1:1 ratio to either the supervised multicomponent exercise group or the health education control group. Before randomization, participants will be stratified according to frailty status, classified as prefrail or frail based on the EFS, to promote a balanced distribution of frailty levels between groups.

The randomization process will be performed using the online platform Research Randomizer by an independent researcher who will not participate in participant recruitment, assessments, intervention delivery, or data analysis [27]. Allocation concealment will be ensured through sequentially numbered, opaque, sealed envelopes prepared in advance by the independent researcher.

After baseline assessments, the next sequential envelope will be opened by a research assistant who is not involved in outcome assessment procedures. Participants will then be informed of their assigned group and referred to the corresponding intervention procedures.

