### Sample Size

Sample size estimation was performed using G*Power software (version 3.1.9.7; Heinrich Heine University) [48,49]. The calculation was based on the primary outcomes of functional capacity and fall risk, assessed by the 6MWT and the TUGT, respectively. An effect size of 0.56 was adopted based on the findings of Espejo-Antúnez et al [50], who evaluated the effects of a 12-week exercise intervention on functional capacity and fall-related outcomes in older adults. Assuming a 2-group parallel RCT design, a statistical power of 95%, and a significance level of 5% (*α*=.05), the minimum required sample size was estimated at 35 participants per group. Therefore, the study was designed to include 70 participants, with 35 allocated to each group. Because recruitment will be conducted among community-dwelling older adults regularly attending activities at the CONVIVER Community Center, and eligibility will depend on screening procedures, the final sample will be obtained through convenience sampling. Recruitment feasibility was considered during the planning phase to ensure attainment of the target sample size.

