### Strengths and Limitations

This study presents some limitations that may impact the generalizability of its results. The selection of participants through convenience sampling, restricted to older adults attending the CONVIVER Community Center, may not represent the broader older population of Rio Verde. Additionally, the exclusion criteria, such as limiting participation to individuals with some degree of frailty, restrict the applicability of the findings to a specific group. Voluntary participation may introduce bias, favoring individuals who are more motivated, which could influence the intervention outcomes. Another factor to consider is the intervention frequency, conducted only twice a week, which may reduce the program’s effects compared to protocols with a higher training volume. Furthermore, the study does not strictly control external factors, such as other physical activities performed by participants, which could impact the results. Although randomization is stratified by frailty status to reduce imbalance between groups, residual imbalance in other baseline characteristics, such as age, sex, comorbidities, and functional capacity, may still occur due to the relatively small sample size and single-center design.

Another potential limitation is the possibility of contamination between groups. Because participants will be recruited from the same community center and may interact during routine activities outside the study sessions, information and experiences related to the interventions may be shared between participants allocated to different groups. Although educational workshops and exercise sessions will be conducted separately and participants will be instructed not to discuss the intervention content with other participants, some degree of contamination cannot be completely excluded. This may reduce the observable differences between groups and potentially underestimate the true effect of the intervention.

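### The primary ANCOVA omits the frailty stratum by which the trial randomises, which makes the test conservative and can cost power

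*Protocol article*

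**What the plan says.** Under Randomization, the protocol article states that before allocation "participants will be stratified according to frailty status, classified as prefrail or frail based on the EFS", the purpose being "to promote a balanced distribution of frailty levels between groups". The ratio is 1:1. Strengths and Limitations relies on this feature again: "Although randomization is stratified by frailty status to reduce imbalance between groups", and goes on to concede possible imbalance in other characteristics.

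Under Statistical Analysis, the primary model for both primary outcomes is an ANCOVA "comparing postintervention values between groups while adjusting for the corresponding baseline values". No other covariate is named, and frailty status does not appear anywhere in that section.

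On how allocation is carried out, Randomization mentions "sequentially numbered, opaque, sealed envelopes prepared in advance by the independent researcher" and says that after baseline assessment "the next sequential envelope will be opened by a research assistant who is not involved in outcome assessment procedures". It does not say how the strata enter this procedure.

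**The concern.** Stratified allocation makes the arms alike in their frail/prefrail mix, so differences between strata largely drop out of the treatment contrast. An analysis that ignores the stratum still counts those differences as residual noise. The reported standard error is then larger than the true one, the test rejects too rarely under the null, and power is lost. The design pays for precision that the analysis does not collect.

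This is not a detail left to an analysis plan that is not shown. The article itself fixes the primary model and names its covariate, and that covariate list does not match the design.

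Power is not plentiful here. If the planning effect of 0.56 is read as a standardised mean difference, 35 per group gives about 64% in a two-sided two-sample t test, against the 95% stated under Sample Size. That is a separate matter, but it is a reason not to give precision away.

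**Working it through.** The protocol has no figure of its own on this point to reproduce, so the check has two parts.

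**1. Design against model.** Stratification factor (Randomization; Strengths and Limitations): frailty, two levels. Covariates in the primary model (Statistical Analysis): the baseline value of the outcome. The stratum is in the first and not in the second.

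**2. What the omission costs.**

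From the protocol: 35 per arm, 1:1, two strata, alpha 5%.

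Assumed, because the protocol gives no figure:
- proportion frail p = 0.5;
- residual stratum effect g, the frail-prefrail difference left after baseline adjustment in units of the residual SD, from 0.3 to 1.0;
- treatment effect 0.7 residual SD. For orientation, if 0.56 is a standardised mean difference and the baseline-outcome correlation were 0.6, it becomes 0.56/√(1 − 0.6²) = 0.56/0.8 = 0.70.

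With arms balanced within strata, the true standard error of the treatment contrast does not depend on g. The model without the stratum estimates a residual variance that is too large by the factor

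k² = 1 + g²p(1 − p) = 1 + g²/4.

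Its t statistic is therefore too small by the factor k. In effect the critical value rises from 1.996 (t, 67 df) to 1.996k. Then:

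- type I error ≈ P(|t| > 1.996k), 67 df;
- power ≈ P(t′ > 1.996k), where t′ is noncentral t with noncentrality 0.7 × √(35/2) = 2.928;
- with the stratum in the model (66 df), power is 82.3% whatever g is.

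| g (residual SD) | k² | k | 1.996k | Type I error, stratum omitted | Power, stratum omitted | Loss against 82.3% |
|---|---|---|---|---|---|---|
| 0 | 1.0000 | 1.000 | 1.996 | 5.0% | 82.3% | 0 |
| 0.3 | 1.0225 | 1.011 | 2.018 | 4.8% | 81.7% | 0.6 points |
| 0.5 | 1.0625 | 1.031 | 2.057 | 4.4% | 80.7% | 1.6 points |
| 0.8 | 1.1600 | 1.077 | 2.150 | 3.5% | 78.0% | 4.2 points |
| 1.0 | 1.2500 | 1.118 | 2.232 | 2.9% | 75.6% | 6.7 points |

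Simulation under the same assumptions (40,000 runs) agrees. With the stratum omitted, type I error is 4.8%, 4.3%, 3.5% and 2.8% for g = 0.3, 0.5, 0.8 and 1.0, and power is 81.9%, 81.0%, 78.2% and 75.3%, against about 82.5% with the stratum. A further simulation of 20,000 runs gave type I errors of 4.5% and 2.9% at the two ends, and power of 81.4% against 82.0% at 0.3 SD and 74.4% against 81.5% at 1.0 SD.

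**The case against.** The best defence is that the omission may cost almost nothing. Baseline 6MWT or TUGT is already in the model, and the Edmonton Frailty Scale itself scores functional independence and functional performance, so the baseline value may carry most of what frailty says about the outcome. The protocol gives no residual effect of frailty, and at 0.3 SD or below the loss is trivial. There is also no bias and no excess of false positives. All of this stands. It limits the size of the point but not its direction, and it gives no reason to leave the stratum out.

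A reader might also infer from the envelope text that all participants draw from one common sequence, so that the stratification would exist in name only. The document does not support that. It never says there is a single series. Taking the next numbered envelope is equally compatible with one series per stratum, and Strengths and Limitations repeats that randomisation is stratified. Separate lists and blocks are details that a condensed article may leave to the full protocol. Figures for frailty imbalance under a single list would describe a procedure that the document does not state, so none are given here. What remains is that the Randomization section does not show how the strata enter the procedure, and one clause would settle it.

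**Conclusion.** The point holds for the analysis model: the primary ANCOVA leaves out the factor by which the trial stratifies. With working stratification, the consequence is a conservative test and lost power, not bias or alpha inflation. Assuming half the sample frail, 35 per arm and a treatment effect of 0.7 residual SD, the cost runs from negligible at a residual stratum effect of 0.3 SD (type I error about 4.7-4.8%, loss under 1 point) to about 7 points of power at 1.0 SD (about 75% against 82%, type I error about 2.8-2.9%). Where the trial will fall in this range cannot be told from the protocol, and if the baseline value absorbs the frailty effect, nothing is lost. The change is worth making because it costs next to nothing and matches the analysis to the design. The envelope wording calls for clarification only and is not evidence that the stratification fails.

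**What to change.** In Statistical Analysis, specify the primary model for each of 6MWT and TUGT as: postintervention value = group + baseline value of the same outcome + frailty stratum (prefrail/frail, as used at randomisation).

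In Randomization, add a clause saying that the next envelope is taken from the series for the participant's own frailty stratum, if that is the procedure.

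The cost is one residual degree of freedom (67 to 66) and two short edits. The article states that recruitment has not started and no outcome data exist, so both can still be fixed without knowledge of the data.

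### The labels small 0.2, medium 0.5 and large 0.8 are set for eta squared as well as Cohen d, but fit only Cohen d

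*Protocol article*

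**What the plan says.** The Statistical Analysis section of the protocol article states the interpretation rule in one sentence: "Effect sizes will be calculated using eta squared (η²) and Cohen *d* and interpreted as small (0.2), medium (0.5), or large (0.8". Both measures are the subject of that sentence and a single series of three cut-offs follows. No other part of the article gives eta squared its own cut-offs or confines these three to Cohen d.

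The same section fixes the main model: "The primary analytical model for the 2 primary outcomes (6MWT and TUGT) will be an analysis of covariance", comparing post-intervention values between groups with adjustment for baseline. It also plans paired and independent t tests or their rank-based counterparts. It does not say which effect size goes with which analysis, or whether eta squared means the plain or the partial version.

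The Randomization section says that "participants will be randomly allocated in a 1:1 ratio". The Sample Size section says that "An effect size of 0.56 was adopted" and does not name the metric of that figure.

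**The concern.** Cohen d is a mean difference divided by an SD and has no upper limit. Eta squared is a proportion of variance and lies between 0 and 1. The same three numbers cannot mark the same three sizes of effect on both. The figures 0.2, 0.5 and 0.8 are the usual benchmarks for d. Applied to eta squared, they give one result two conflicting descriptions.

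What is at stake is how the results for the two primary outcomes, the 6-minute walk and the Timed Up and Go, are put into words. A reader given the eta squared label would think the effect smaller than the Cohen d label says. With both labels available under the stated rule, the wording could also be chosen after the results are known.

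**Working it through.** **Inputs.** Cut-offs 0.2/0.5/0.8 for both measures (Statistical Analysis); two groups, 1:1 (Randomization); 35 per group, 70 in total (Sample Size); ANCOVA adjusted for baseline (Statistical Analysis). The article gives no baseline-to-post correlation, so ρ is assumed and run from 0 to 0.9.

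**Step 1. From d to plain eta squared.** For two equal groups, η² = d²/(d² + 4).

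- d = 0.2: 0.04/4.04 = 0.010
- d = 0.5: 0.25/4.25 = 0.059
- d = 0.8: 0.64/4.64 = 0.138

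The stated cut-offs are therefore not reproduced on the eta squared scale. With the sample degrees of freedom for N = 70, the 4 becomes 4 × 68/70 and d = 0.8 gives 0.141, which changes nothing.

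**Step 2. From plain eta squared back to d.** d = 2√(η²/(1 − η²)).

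- η² = 0.2: 2√0.25 = 1.0
- η² = 0.5: 2√1 = 2.0
- η² = 0.8: 2√4 = 4.0

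**Step 3. Partial eta squared from the ANCOVA.** With d on the unadjusted SD, partial η² = (d²/4)/(d²/4 + 1 − ρ²).

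| ρ (assumed) | d = 0.2 | d = 0.5 | d = 0.8 |
|---|---|---|---|
| 0 | 0.010 | 0.059 | 0.138 |
| 0.5 | 0.013 | 0.077 | 0.176 |
| 0.6 | 0.015 | 0.089 | 0.200 |
| 0.7 | 0.019 | 0.109 | 0.239 |
| 0.8 | 0.027 | 0.148 | 0.308 |
| 0.9 | 0.050 | 0.248 | 0.457 |

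A large d reaches the small cut-off from ρ of 0.6 and does not reach medium in this range. It would do so only when 1 − ρ² falls to 0.16, that is at ρ = √0.84 = 0.92. A medium d reaches small only when 1 − ρ² falls to 0.25, that is at ρ = √0.75 = 0.87. A small d never gets there. All three benchmarks carry the wrong label at every correlation in the table.

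If d is instead standardised by the baseline-adjusted SD, it equals d/√(1 − ρ²). The formula for partial η² then becomes the one in Step 1, and the figures of Steps 1 and 2 apply unchanged.

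**Step 4. The planning effect.** Read as Cohen d, 0.56 gives 0.3136/4.3136 = 0.073, below the stated cut-off for small although d = 0.56 is medium. This is conditional on the metric. Read as Cohen f, it would give 0.3136/1.3136 = 0.239, above 0.2.

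**The case against.** **The authors may have meant the labels for d only.** The cut-offs directly follow the mention of Cohen d, and a condensed article may have dropped a second set. This is possible, but the sentence as written covers both measures. If d alone was meant, eta squared has no scale. Either reading calls for the same edit.

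**The plain conversion may be the wrong one for an ANCOVA.** This stands in part. A reader might infer that a large effect would always be reported as less than small, or that d of 1.0, 2.0 and 4.0 is always needed to reach the three cut-offs. With d on the unadjusted SD, both statements hold only for plain eta squared. With partial eta squared and a correlation of 0.6 or more, a large d would be called small. That softens the error without removing it.

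**The planning effect proves little.** This also stands. A reader might infer that the trial's own target effect falls below small. The article does not name the metric of 0.56, and the reading as f reverses the result. Nor does the sample size settle it. At 95% power and 5% alpha, an independent t test needs 84 per group two-sided (70 one-sided) if 0.56 is d, and 22 per group two-sided if it is f. Neither gives the stated 35.

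**Nothing inferential depends on the labels.** This is right. A reader might infer that nearly every result would be misclassified or that the trial's conclusions are at risk. The article does not support that: labels on Cohen d are unaffected, eta squared is not tied to any one analysis, and no test or success criterion uses the labels.

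**Conclusion.** The rule is wrong as written for one of the two measures it names. For plain eta squared in 1:1 groups, the values that match d of 0.2, 0.5 and 0.8 are 0.010, 0.059 and 0.138, so all three lie below the cut-off stated for small. For partial eta squared, with d on the unadjusted SD and ρ assumed between 0 and 0.9, a large d is called small at best.

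The conclusion rests on the two-group comparison with equal allocation; it does not address effect sizes for the paired within-group tests. It does not depend on the metric of the planning effect. The consequence is limited to how effects are described: tests, P values and the sample size do not change. It is still worth correcting, because the rule governs how both primary outcomes may be worded and recruitment has not started.

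**What to change.** Rewrite the one sentence in Statistical Analysis so that:

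- 0.2/0.5/0.8 apply to Cohen d only;
- eta squared has its own cut-offs of about 0.01/0.06/0.14;
- it says whether eta squared or partial eta squared will be reported.

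The third item is needed because 0.01/0.06/0.14 match the d cut-offs only for plain eta squared in equal groups. With partial eta squared and d on the unadjusted SD, labels could still disagree: at ρ = 0.8, d = 0.5 gives 0.148, which would be large by the new cut-offs. The cost is one sentence, with no change to design, data collection or analysis.

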**Figure 4. F4:**
[figure not shown]
Schedule of assessments for screening, sample characterization, and primary outcomes. CFVI-20: Clinical-Functional Vulnerability Index-20; EFS: Edmonton Frailty Scale; FES-I: Falls Efficacy Scale-International; GDS-15: Geriatric Depression Scale-15; IPAQ: International Physical Activity Questionnaire; MMSE: Mini-Mental State Examination; 6MWT: 6-Minute Walking Test; TUGT: Timed Up and Go Test.

At baseline, sociodemographic and clinical data will be collected, along with assessments of depressive symptoms (Geriatric Depression Scale-15 [GDS-15]), muscle mass (calf circumference), physical activity level (International Physical Activity Questionnaire [IPAQ]), fear of falling (Falls Efficacy Scale-International [FES-I]), and clinical-functional vulnerability (Clinical-Functional Vulnerability Index-20 [CFVI-20]) to characterize the older adults. The primary outcomes, namely functional mobility assessed by the Timed Up and Go Test (TUGT) and functional capacity assessed by the 6-Minute Walk Test (6MWT), will be evaluated at baseline and reassessed after the 12-week intervention period (T2).

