### Safety Assessment and Withdrawal

Participant safety will be monitored throughout the intervention period by the research team and supervising physiotherapists. Any AEs potentially associated with the exercise sessions or assessment procedures, including dizziness, pain, excessive fatigue, musculoskeletal discomfort, falls, cardiovascular symptoms, or any other clinical complaints, will be immediately documented and evaluated.

If a participant develops any AE or clinical instability during the intervention period, exercise participation will be temporarily interrupted, and the participant will be closely monitored by the research team. When necessary, the participant will be referred for medical evaluation before resuming study activities. In cases where symptoms persist, recur after reintroduction of the intervention, or compromise participant safety, the participant may be withdrawn from the study after clinical assessment by the investigators. All AEs and safety-related occurrences will be systematically recorded in standardized monitoring forms throughout the trial period.

Participants will be free to discontinue their participation at any moment and for any reason, including the option to request the removal of their data from the study. Individuals will be considered withdrawn if they formally request to leave the trial or are lost to follow-up. Participants allocated to the intervention group will be classified as withdrawn if they discontinue participation in the supervised exercise program. Participants allocated to the control group will be classified as withdrawn if they discontinue participation in the educational workshops before the completion of the study.

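### Agreement between complete-case and multiply imputed results says little about outcome-related dropout that differs between the arms

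*Protocol article*

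**What the plan says.** All of the following is in the protocol article.

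- **Model** (Statistical Analysis): the primary analysis of the 6MWT and TUGT is an ANCOVA "comparing postintervention values between groups while adjusting for the corresponding baseline values". Under Assessment Procedures, each outcome is measured once at baseline and once after 12 weeks.
- **Missing data** (Statistical Analysis): "Missing data will initially be explored to determine the pattern and mechanism of missingness". Then: "When appropriate, missing outcome data will be handled using multiple imputation methods based on chained equations". The variables in the imputation model are not named.
- **Robustness** (Statistical Analysis): "Sensitivity analyses will be conducted to compare the results obtained from complete-case analyses and imputed datasets", with the purpose given as "in order to evaluate the robustness and consistency of the findings". The only other sensitivity analysis concerns adherence: "per-protocol analyses will be performed as secondary sensitivity analyses to assess the influence of adherence to the intervention on study outcomes".
- **Withdrawal** (Safety Assessment and Withdrawal): "In cases where symptoms persist, recur after reintroduction of the intervention, or compromise participant safety, the participant may be withdrawn from the study". Stopping the exercise programme counts as withdrawal in the intervention arm, and stopping the workshops counts as withdrawal in the control arm.
- **Follow-up** (Participants; Statistical Analysis): non-adherent participants stay in the intention-to-treat analysis where possible, and the aim is to reassess everyone at 12 weeks where possible.

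**The concern.** A sensitivity analysis is informative when it changes the assumption that may be wrong. For missing outcomes, that assumption is that participants without a 12-week value would have done as well as similar participants who have one. Complete-case ANCOVA makes it given group and baseline. Multiple imputation makes it given whatever is in the imputation model. If that model adds little to group and baseline, the two analyses share the assumption and will agree whether or not it is true.

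The case that matters is exercisers leaving because of symptoms or poor tolerance who would also have walked less far or moved more slowly at 12 weeks. Both analyses would then overstate the benefit, and their agreement could be reported as robustness.

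The sentence on the mechanism adds to this. Observed data can show the pattern of missingness and which recorded variables predict it. They cannot separate missing at random from missing not at random, because that depends on the values not seen.

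**Working it through.** The plan has no figure on missing data to reproduce, so the check asks whether the stated comparison can tell a biased result from an unbiased one.

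**Inputs from the article.** 35 per arm and an effect size of 0.56, read as a standardised mean difference (Sample Size); ANCOVA on group and baseline; one follow-up value per outcome.

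**Assumptions not in the article.** Baseline to 12-week correlation 0.7; the attrition rates; how those lost differ from those seen. Effects are in SD units, with higher meaning better.

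**Step 1: why the two coincide.** Let b be the ANCOVA coefficients from observed cases, so X_obs′y_obs = X_obs′X_obs b. Imputation from group and baseline fills the missing values, on average, with X_mis b. Refitting to the completed data solves

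(X_obs′X_obs + X_mis′X_mis) β = X_obs′y_obs + X_mis′X_mis b,

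which gives β = b. With many imputations from the same linear model, the imputed estimate is the complete-case estimate.

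**Step 2: size of the shared bias.** If a share p of an arm is missing and those participants are δ worse than predicted, the observed arm mean is too high by p × δ. For the contrast:

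bias = p_E δ_E − p_C δ_C (E = exercise, C = control).

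With no informative dropout in controls:

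- 0.10 × 0.25 = 0.025, about 0.03 SD
- 0.20 × 0.50 = 0.10 SD (0.10 / 0.56 = 18% of the design effect)
- 0.25 × 0.75 = 0.1875, about 0.19 SD

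If p and δ are equal in both arms, the bias is 0.

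A simulation of the middle case (1,000 trials, 50 imputations, 20% missing exercisers, 10% missing controls) gave 0.459 on full data, 0.558 complete case and 0.559 imputed. The bias is 0.558 − 0.459 = 0.099, while the two planned analyses differ by 0.008 on average.

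**Step 3: does agreement discriminate?** A separate simulation used 2,000-3,000 trials per scenario and 20 imputations, with about 20% missing in controls and 22-25% in exercisers (25% in both arms in the fourth row). The true effect is 0.56 except in the third row. The extra predictor is described by its correlation with the part of the 12-week outcome that group and baseline do not explain.

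| Exercise-arm dropout depends on | Extra predictor in imputation | Full data | Complete case | Imputed | Mean absolute gap |
|---|---|---|---|---|---|
| baseline only | none | 0.562 | 0.560 | 0.561 | 0.017 |
| outcome | none | 0.567 | 0.791 | 0.792 | 0.016 |
| outcome, true effect 0 | none | 0.001 | 0.229 | 0.229 | 0.016 |
| outcome, same in both arms | none | 0.570 | 0.565 | 0.565 | 0.016 |
| outcome | 0.2 | 0.564 | 0.788 | 0.781 | 0.023 |
| outcome | 0.3 | 0.561 | 0.789 | 0.770 | 0.030 |
| outcome | 0.5 | 0.558 | 0.787 | 0.734 | 0.059 |
| outcome | 0.8 | 0.549 | 0.777 | 0.640 | 0.139 |
| the extra predictor | 0.2 | 0.558 | 0.603 | 0.558 | 0.051 |
| the extra predictor | 0.5 | 0.559 | 0.672 | 0.558 | 0.114 |

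Rows 1 and 2 are decisive. The gap is 0.017 when both analyses are right and 0.016 when both are about 0.22 too high (0.791 − 0.567 = 0.224). The last six rows set the limit: a predictor strongly related to the outcome or to dropout can separate the two analyses. Where dropout depends on the outcome itself, both stay above the truth even then.

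**The case against.** A reader might infer that the two analyses always rest on the same assumption and are bound to agree. The article does not support that. It names no imputation variables, and the trial records several candidates: attendance, adverse events, and baseline frailty, mood, fear-of-falling and vulnerability scales. If one of these drives dropout and is in the imputation model, the comparison is informative (0.672 against 0.558). This part of the objection stands.

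A reader might also infer that the trial's result will be biased by a fifth of an SD. That does not follow either. The article states no expected attrition, every bias figure above comes from assumed inputs, and the stated aim is to reassess everyone, including non-adherers. Stopping exercise therefore need not mean a missing outcome. Withdrawal rules exist for both arms, and informative dropout of equal strength in each leaves the contrast almost unbiased.

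Two further points are fair but do not remove the concern. First, the text claims robustness in general, not robustness to informative dropout. But it is the only missing-data check stated, and a reader of the results would take it as covering the main threat. Second, imputation details and analyses that depart from missing at random are often left to an analysis plan, and one may exist. The point here is what the article does state: it gives the robustness role to a comparison that can fill it only under conditions it does not set, and it says the mechanism can be determined.

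**Conclusion.** The concern holds in a limited form. With one follow-up value and baseline-adjusted ANCOVA, agreement between complete-case and imputed results is weak evidence of robustness unless the imputation model contains strong predictors beyond group and baseline. It cannot rule out bias from outcome-related dropout that differs by arm. Such dropout is plausible because symptoms that recur when exercise resumes can lead to withdrawal, and controls do not exercise; it is not certain.

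The illustrative bias of 0.03-0.19 SD assumes 10-25% missing exercisers who are 0.25-0.75 SD worse than predicted, with no informative dropout in controls. It shrinks towards zero as the two arms become alike or as reassessment becomes complete. The sentence on determining the mechanism claims more than observed data can deliver and needs rewording whatever the attrition.

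**What to change.** - Keep multiple imputation under missing at random as the main handling. Name the imputation variables and include recorded auxiliaries such as attendance, adverse events and the baseline scales.
- Keep the complete-case comparison, but describe it as a check within missing at random only.
- Add a prespecified delta-adjusted (tipping-point) analysis. Worsen the imputed 12-week values by arm in fixed steps (6MWT down, TUGT up) and report the shift at which the conclusion changes.
- Optionally, impute missing exercise-arm values from the control-arm distribution. This needs a separate imputation run.
- Replace the promise to determine the mechanism with *describe the pattern and observed predictors of missingness*.

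The cost is a paragraph in the analysis section, a little more analysis work and possibly a less favourable robustness statement. No new data are needed. The article reports that recruitment had not started at submission, so a change made before it starts would be fully prespecified.
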